### Eligibility Criteria and Recruitment of Facilities

#### Overview

The intervention facilities were purposively identified by the National Department of Health (NDOH) as sites with MNH service performance and capacity below the national average in South Africa. In addition, the selected intervention sites reflect the clinical and referral pathways and represent both urban and rural settings. For objectives 2 and 3, the comparison districts were purposively selected to match the intervention districts in as many respects as possible, including iMMR, stillbirth rate, neonatal mortality rate, sociodemographic characteristics, service organization, and setting (rural, urban, and periurban), and to provide the NDOH standard of care. In total, 3 facilities (2 district hospitals and 1 regional hospital) in the comparison district were selected and matched to the intervention district based on the total number of births. Data collection for objectives 2 and 3 is conducted in 18 hospitals (15 district- and 3 regional-level hospitals). Objective 4b is being conducted in 15 hospitals, purposively selected from the 21 intervention facilities.

#### Participant Inclusion Criteria for Maternal Interview Shortly After Delivery (Objective 2) and Data Abstraction From Maternity Records (Objective 3)

To assess patient experiences of care and determine the quality of maternal care, participants who are aged ≥18 years, has a pregnancy diagnosis, who accessed care within the participating health facilities during their pregnancy, or who are within 1 week post partum are eligible. Research assistants will screen for eligibility using specified inclusion criteria. All women meeting any of the following criteria will be eligible: (1) pregnant women at ≥36 weeks gestation without any complications, (2) pregnant women at ≥36 weeks gestation with HIV before pregnancy and on antiretroviral therapy and diagnosed with HIV at first antenatal visit, (3) positive repeat antenatal HIV test following the first negative antenatal HIV test, (4) pregnant women at ≥36 weeks’ gestation with eclampsia, (5) pregnant women at ≥36 weeks’ gestation with primary postpartum hemorrhage, (6) postpartum women at ≤7 days with a premature baby, (7) postpartum women at ≤7 days with a healthy term baby, and (8) postpartum women at ≤7 days with a baby in the ICU. The medical records of eligible cases will be retrieved for a thorough review at hospital discharge or on transfer to another hospital.

Data collectors will conduct daily visits to maternity wards to recruit maternal participants and determine the antenatal quality of care during the pandemic era. During the daily visit, the admission and maternity registers are screened for participants who meet the study inclusion criteria. Stable women with recent deliveries are approached by an interviewer for recruitment before leaving the facility and are interviewed in a private space to ensure confidentiality or via telephones if on-site interviews are not possible. Women are excluded from participation if they are aged <18 years, delivered at home or on the way to the facility, are acutely ill in the ICU or with life-threatening conditions, or are emotionally distressed. Women whose infants are admitted to the ICU or who experienced a stillbirth or neonatal death will be approached for interview, and if they agree, they will be interviewed at a time that suits the mother.

#### Participant Inclusion Criteria (Objective 4)

At the macrolevel (provincial and national) and mesolevel (subdistrict and district; objective 4a), the study team will purposively recruit subdistrict, district, and area managers and those specifically responsible for managing maternal and neonatal care services across subdistricts, districts, provinces, and areas. At the microlevel (facility; objective 4b), we include all QI advisers, that is, persons who provide QI expertise and support to participating facilities’ health workers who are organized in QI teams as well as the operational managers of the sampled facilities.

### Procedures

#### Conceptual Framework

Our initial hypothesis was that the QI methodology will enhance the quality of MNH care by creating an enabling environment for leadership and governance to flourish, ensuring that clinical processes are delivered safely and reliably. A key component of the QI approach is ensuring respectful care and support for patients. We further hypothesize that optimizing the environment and processes will improve the health care system, leading to improved health outcomes and patient experience of care. Our underlying causal assumptions are that QI will empower macro- and mesolevel management and microlevel health workers to drive and implement change.

Implicit assumptions are staff participation in QI training, a facility QI team that continues QI activities throughout study implementation, and a leader within that team with continuity of participation are integral to its success. At the start of the intervention, the Mphatlalatsane Initiative implemented the Institute for Healthcare Improvement model for improvement as a framework to guide its implementation strategy [10]. The strategy involves the identification of a specific goal for improvement and a plan to measure progress and then commences with change ideas that may lead to improvement over a short duration. As the change ideas are refined and successfully applied, the interventions are broadened to increase the magnitude of the changes. The Institute for Healthcare Improvement stresses initiating improvement on a small scale and leveraging the obtained knowledge to plan for wider implementation and eventual scale-up. Additional assumptions included that other competing programs or priorities implemented by the NDOH would not be conducted in the intervention catchment areas. However, the COVID-19 pandemic disrupted QI team functioning. The consortium partners prioritized the immediate needs of facilities, which broadened the initial intervention scope (described below under *Intervention Dose* section) of the Mphatlalatsane Initiative.

A framework of mesolevel (district and subdistrict) enabling environments was developed a priori, which included factors of distributed leadership and buy-in, area-based mechanisms of service delivery coordination and review, referral and outreach systems, and the allocation of resources in response to identified needs at the facility level.

#### Intervention Package

The Mphatlalatsane Initiative initially aimed to improve the quality of maternal and neonatal care in the participating facilities through QI activities. A QI adviser has been appointed in each catchment area to manage and support these teams. We anticipate that these teams will become nodes of “learning practices,” with team members pooling their efforts and skills toward solving targeted service problems [18]. We view the respective microlevel health systems, in which the QI teams function, as social systems, with the agency of staff and the relationships, existing and to-be-established, within these systems [19], as key to understanding the teams’ performance. The evaluation and intervention teams are independent to minimize bias. The intervention design of in-person support shifted based on facility responses during the COVID-19 pandemic. Initial attempts to use digital platforms to support QI teams were unsuccessful, and QI advisers subsequently supported QI teams through telephonic messages and calls. Other design changes included providing emotional support and guidance and improving the efficiency of supply chain management for infection control and personal protective equipment. Once the acute demands were met, the Mphatlalatsane intervention was revised to mitigate the interruptions in access to routine MNH services.

QI activities comprise the repeated and rapid implementation of Plan-Do-Study-Act (PDSA) cycles [20,21]. The *Plan* refers to problem identification and development of solutions; the *Do* refers to implementation of the solutions; the *Study* refers to the evaluation of effects of the solutions and then *Acting* on the outcome of the evaluation by adopting, adapting, or rejecting the solutions [20,21]. QI teams have been established in each participating facility to engage maternal and neonatal staff in relevant PDSA activities [21,22].

#### Comparator

Health care providers in the control district facilities continue to provide the NDOH standard of care to antenatal and postnatal attendees as per the policy and guidelines. The usual training for staff involves weekly 1-hour in-service training on current evidence-based guidelines. The usual training does not include a coaching or mentoring component and is not a data-driven process for evaluating the implementation of evidence-based guidelines.

### Data Sources

#### Objective 1

Mortality data from 2017 to 2022 were extracted from the District Health Information System (DHIS; Table 1).

**Table 1 table1:** Mphatlalatsane data sources.

Objective	Data source	Variable or theme	Level of analysis
1	DHIS^a^	Mortality data (maternal, neonatal, and stillbirths) extracted quarterly from 2019 to 2022	District and facility
2	Participant interview shortly after delivery in regional or district hospitals	The effect of the QI^b^ intervention over time on patients’ experience of the quality of antenatal and postnatal health care services from 2021 to 2022	Individual
3a	Maternal records from regional or district hospitals	Facility audit of maternal records will be conducted to measure adherence to clinical protocols on normal pregnancy, HIV, eclampsia, and postpartum hemorrhage from 2021 to 2022	Individual
3b	Structured observation checklists will be interviewer administered in selected facilities based on the Newborn QI Toolkit norms and standards for newborn care, which were developed to collect data in each facility [23]	Availability of equipment and supplies Availability of guidelines or policies Distribution and availability of drugs Data quality and use Staffing Infrastructure	Facility
4a	Semistructured interviews and FGDs^c^ with the QI advisers, operational managers, and management staff	Stakeholder analysis: coordination processes, nature and quality of social networks, decision-making processes, formal and informal communication, and collaboration between key actors. We will set up monthly individually open-ended debriefing meetings with the QI advisers, and they will reflect on their work and engagement with the QI teams. We will also review program documentation, including the documentation that the QI teams will generate during the PDSA^d^ cycles. We will also conduct other program meetings at the macro- and mesolevels.	National, provincial, district and subdistrict
4b	Interviews and FDGs with QI teams QI team surveys QI adviser debriefings Program documentation	QI advisers, teams, and facility managers: setting up, management structures, systems of communication, translation of their PDSA cycles into everyday practices, climate for QI activities, relational dynamics in the teams, ownership of change, resource use, experiences, and perceptions of implementation changes over time, perceived benefits, and challenges of the QI work in their facilities. QI team outcomes: packaging learning practices for scale-up and identify the “leverage points” for change.	Facility

^a^DHIS: District Health Information System.

^b^QI: quality improvement.

^c^FGD: focus group discussion.

^d^PDSA: Plan-Do-Study-Act.

#### Objective 2

In-person or telephonic interviews were conducted with pregnant women shortly after delivery to measure participants’ subjective experiences of care. The survey used a 5-point Likert scale based on a prior study of maternal patient satisfaction with services in Tanzania [24]. Data collectors administered paper-based surveys at the midline, which were then captured using REDCap (Research Electronic Data Capture; Vanderbilt University) software.

#### Objective 3a

Data collectors took photographs or abstracted data from maternal records, which were then entered into the REDCap database. Facility audit of maternal records were conducted by an experienced nurse to measure adherence to the guidelines and implementation of care. Data were collected at a single time point within 1 week of delivery.

#### Objective 3b

Interview-administered structured observation checklists were completed in all selected facilities based on the Newborn QI Toolkit [23] norms and standards for newborn care.

Data were also collected using a series of checklists to determine the quality of record keeping for the newborns. Staff members in the neonatal unit were requested to provide the clinical records of a sample of newborns with the following conditions: (1) low birth weight, (2) infection, and (3) asphyxia. A review of these records was conducted to determine the quality of record keeping. Data collection for objective 3 was at the end line (approximately June 2022 to August 2022).

#### Objective 4a

Semistructured interviews and focus group discussions (FGDs) were conducted with the QI advisers, QI teams, operational managers, and management staff at the subdistrict, district, and provincial levels.

#### Objective 4b

The data collection comprised (1) interviews and FGDs with the QI team leaders and members, (2) digital surveys to leaders and teams to assess their performance, (3) regular debriefings with the advisers, and (4) a review of program documentation. The debriefings and documentation reviews commenced in February 2020, and the interviews, FGDs, and surveys began in May 2021. As of November 2022, we conducted 32 interviews with leaders and 51 interviews or FGDs with team members.

### Sample Size

#### Objective 1

Using the number of deliveries and maternal and perinatal deaths in 9 regional and district facilities in the chosen intervention catchment areas (the Eastern Cape, Limpopo, and Mpumalanga) between 2018 and April 2019, rates were found to be 115.4 maternal deaths per 100,000 live births, 14.4 neonatal deaths per 1000 live births, and 22.5 stillbirth births per 1000 facility births. For this study, an intraclass correlation estimator from a random intercept logistic regression model was used. Using the average facility size (based on deliveries in the intervention catchment areas during the baseline period), the variance inflation factor was estimated at 1.0, 1.4, and 1.3 for the maternal mortality ratio, neonatal mortality rate, and stillbirth rate, respectively. To test the hypothesis that there was no improvement against a 50% increase in the baseline, with 80% power at a 5% two-sided significance level, the number of live births would be 40,524 and 4512 for testing maternal and neonatal mortality rates and 2666 for stillbirth rates. We will observe at least 41,000 deliveries pooled across the 3 catchment areas over a 3-year period to have minimum power for all outcome comparisons. The same would accrue in the control facilities.

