### Study Design

We are conducting a mixed methods implementation science type 2 hybrid effectiveness design to study the intervention effect (objectives 1-3) and implementation (objective 4) during the COVID-19 pandemic. Given that the intervention facilities were preselected, the quantitative component will be implemented as a quasi-experimental controlled before-and-after study (nonrandomized assignment of the intervention and comparison groups) to measure the effect of a QI intervention implemented during the COVID-19 pandemic on maternal and neonatal outcomes. Data on the iMMR, neonatal mortality rate, and stillbirth rate will be analyzed from 2019 to 2021, including the time before and during the COVID-19 pandemic in South Africa (objective 1). Study data on maternal experiences of care (objective 2) and maternal and neonatal quality of care (objectives 3a and 3b) were collected between 2021 and 2022. Objective 4 data collection commenced in early 2020 and ended in August 2022.

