
### Statistical Analysis

#### Objective 1

The institution maternal and perinatal mortality indicators will be calculated using DHIS data. Trend in iMMR, neonatal mortality rate, and stillbirth rates (with SE bars) during the pre- and postintervention periods will be disaggregated by intervention arms. RR and 95% CI will be calculated along with data on confounding variables, such as antenatal care coverage before 20 weeks, delivery at health facility access by tar road, deliveries of female participants aged <19 years, and deliveries of female participants aged ≥19 years (derived from total deliveries and deliveries of female participants aged <19 years). The trends in mortality and stillbirths will be compared before the COVID-19 pandemic (January 2019-March 2020) and during the COVID-19 pandemic (April 2020-March 2021) and in the context of the COVID-19 waves. The baseline period (2017-2018) will also be provided. Observed numbers and rates will be determined monthly and quarterly across all 9 provinces in the country and overall. To compare the Mphatlalatsane Initiative intervention and control arm trends in mortality, an interrupted time series regression model using Poisson regression model with Newey-West SEs to account for autocorrelation and possible heteroskedasticity will be used.

#### Objective 2

This study will use quantitative descriptive analyses and exploratory factor analysis to examine associations between sociodemographic characteristics, childbirth characteristics, and maternal participants’ experience of health care quality and the health care facility during the antenatal to postpartum period.

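### The objective 1 sample size is worded as a 50% increase but calculated for a 50% reduction between two groups, and its 80% power does not carry over to maternal mortality in the controlled before-and-after contrast

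*Protocol article*

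**What the plan says.** Sample Size, Objective 1, takes baseline rates from nine facilities in the intervention areas: "rates were found to be 115.4 maternal deaths per 100,000 live births, 14.4 neonatal deaths per 1000 live births". The stillbirth baseline in the same sentence is "22.5 stillbirth births per 1000 facility births". For clustering, the section reports that "the variance inflation factor was estimated at 1.0, 1.4, and 1.3 for the maternal mortality ratio, neonatal mortality rate, and stillbirth rate". The hypothesis is "no improvement against a 50% increase in the baseline, with 80% power at a 5% two-sided significance level". The resulting requirements are 40,524 births for maternal mortality, 4512 for neonatal mortality and 2666 for stillbirth. The section then promises: "We will observe at least 41,000 deliveries pooled across the 3 catchment areas over a 3-year period to have minimum power for all outcome comparisons". It adds that the control facilities would accrue the same number.

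Other sections describe a different effect and a different comparison. The Introduction gives the initial aim as a halving of all three rates in five years. Study Design calls the quantitative component a "quasi-experimental controlled before-and-after study". Statistical Analysis, Objective 1, uses an interrupted time series Poisson regression with Newey-West standard errors, "To compare the Mphatlalatsane Initiative intervention and control arm trends in mortality".

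**The concern.** Two things do not fit together. First, the stated direction of effect is opposite to the aim, and direction matters for sample size: from the same baseline, a 50% rise needs more births than a 50% fall. Second, the calculation has one sample size per group and no time dimension, while the design estimates a change over time in one arm relative to the change in the other. That contrast carries sampling error from four arm-by-period cells instead of two groups.

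The iMMR is the first-listed primary endpoint and by far the rarest event, so extra variance costs most there. The article intends the evaluation to show whether the initiative is effective at improving mortality. Readers who believe iMMR had 80% power could take a non-significant result as evidence that the initiative did not work.

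**Working it through.** **Inputs.** All from Sample Size, Objective 1: baseline risks 0.001154, 0.0144 and 0.0225; variance inflation factors (VIF) 1.0, 1.4 and 1.3; two-sided 5%; 80% power; 41,000 births per arm over 3 years.

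**Step 1: reproduce the stated sizes.** Per group, n = VIF × (1.960 + 0.842)² × [p₁(1−p₁) + p₂(1−p₂)] / (p₁−p₂)², where (1.960 + 0.842)² = 7.849.

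For maternal mortality halved, p₂ = 0.000577, so n = 7.849 × 0.00172934 / 0.000577² = 40,769.

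| Outcome | Stated | 50% reduction | 50% increase |
|---|---|---|---|
| Maternal | 40,524 | 40,769 | 67,913 |
| Neonatal | 4512 | 4,524 | 7,488 |
| Stillbirth | 2666 | 2,670 | 4,402 |

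The reduction column agrees with all three stated figures to within 0.6%. The increase column is 65–68% too high. Continuity-corrected, one-sided, one-sample, Poisson, log-ratio, arcsine and 90%-power versions were also tried, and none reproduces all three figures for an increase. With 41,000 births against 41,000, two-group power for iMMR is 80% for a halving and 59% for a 50% rise.

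**Step 2: power for the arm-by-period contrast, iMMR.** On the log scale, which suits a Poisson model, the variance of the ratio of rate ratios is the sum of 1/(expected deaths) over the four cells, multiplied by the VIF (here 1.0). The effect is |ln 0.5| = 0.693, and power = Φ(0.693/SE − 1.960). The rate is 115.4 per 100,000 everywhere except in the intervention arm after the start, where it is halved.

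With 41,000 births in each cell, expected deaths are 47.3, 23.7, 47.3 and 47.3. SE = √(3/47.3 + 1/23.7) = 0.325, z = 2.13, power 57%. A simulation of 200,000 Poisson data sets gave 56.5%.

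The other rows assume accrual of 41,000/3 = 13,667 births per year per arm.

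| Births per arm, before / after | SE | Power |
|---|---|---|
| 41,000 / 41,000 | 0.325 | 57% |
| 27,333 / 41,000 (2017–2018 baseline, 3 years after) | 0.356 | 49% |
| 20,500 / 20,500 (even split) | 0.460 | 33% |
| 13,667 / 27,333 (1 year before, 2 after) | 0.471 | 31% |
| Unlimited / 41,000 | 0.252 | 79% |

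The last row is a ceiling: with 41,000 births per arm after the start, no length of baseline takes power above the two-group value. About 70,800 births per cell would give 80% on this scale.

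**Step 3: the other two endpoints.** The same formula with VIF 1.4 for neonatal mortality and 1.3 for stillbirth gives more than 99% power for a 50% fall in every row.

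**The case against.** The best defence of the wording is that the increase is a slip for improvement or reduction, and that the arithmetic behind it is sound. That is probably so, and the reproduced sizes support it. The sentence is still wrong as printed.

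On power, one can say that 41,000 is a minimum, that the article does not state how births divide between periods, and that data from 2017 to 2022 were extracted, so the longer windows may apply. All of this stands, and it is why the figures are conditional. It does not restore 80%: every split at the planned minimum falls short. The four-cell calculation is also only an approximation; separate level and slope terms and Newey-West errors were not modelled.

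A reader might infer stronger claims that the document does not support:

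- **Power of about 25%.** This comes from applying January 2019–March 2020 against April 2020–March 2021 to the arm contrast. Statistical Analysis gives those dates for the comparison before and during COVID-19. The arm comparison is a separate sentence without those dates, and the earlier window already contains intervention months.
- **A non-significant iMMR result is more likely than not even if mortality is halved.** This fails in the 57% case.
- **The maternal VIF of 1.0 is wrong.** The article gives no baseline death count against which to judge it. A stable facility effect would also largely cancel in a before-and-after contrast within the same facilities. A higher value is only a sensitivity analysis: 1.4, borrowed from neonatal mortality, would turn 57% into 44%.
- **The other primary endpoints are underpowered.** That requires an effect smaller than the 50% the article targets.

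**Conclusion.** The point holds in two parts. The stated direction contradicts both the section's own numbers and the initiative's aim; this needs no assumption beyond the standard formula. The claim of minimum power for all outcome comparisons is not met for iMMR under the controlled before-and-after contrast. For a 50% fall, power is about 57% in the most generous equal-cell case, about 49% with a two-year baseline and three years after, and about 31–33% if 41,000 births per arm cover both periods.

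Those values rest on accrual at the stated minimum, the article's VIF of 1.0, a log-scale four-cell approximation and an assumed pre/post split. More births than the minimum would raise them. The shortfall concerns iMMR only; neonatal mortality and stillbirth remain well powered for the targeted effect.

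**What to change.** In Sample Size, Objective 1:

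1. Change the increase to a reduction.
2. Say that 40,524, 4512 and 2666 are per-group sizes for a two-group comparison.
3. Add power for the arm-by-period contrast, using the intervention's own before/after window as it will be analysed. State the births per cell, the VIF and the scale. A VIF above 1.0 can be shown as a sensitivity analysis.
4. Withdraw the statement of minimum power for all comparisons as regards iMMR, and say that neonatal mortality and stillbirth are the endpoints adequately powered for a 50% fall.
5. State that iMMR will be reported as an estimate with its confidence interval, and that a non-significant result will not be read as evidence of no effect.

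The cost is a few sentences and a less favourable power figure for iMMR. No extra births or data are needed.
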